### Randomization and blinding

The physician will screen out the patients who meet the eligibility criteria, explain the whole content of the trial and ask the consent to sign the informed consent. Their demographic information, medical history, and medication details will then be collected. We will use an electronic random sequence generator (www.random.org) to randomly assign all of the individuals to one of the three groups in a 1:1:1 ratio. An independent researcher will conceal the allocation using sealed and opaque envelopes, numbered consecutively. In this trial, subjects, assessors, and data analysts are blind to the allocation results. Because this study involves locating therapeutic targets in the cerebral cortex, the intervenor cannot be blind. The treatment and outcome evaluation regimen are depicted in Table 1.

### Procedure

The study will consist of four phases: (1) A baseline assessment involving clinical scales (MAS and FMA-UE) and DTI before the stimulation sessions; (2) Comprehensive rehabilitation, and the corresponding cTBS interventions will be provided once a day, 5 times a week for 4 weeks. Neurophysiological assessments such as H reflex, MEP and SR will be collected before and after the first cTBS treatment at this phase; (3) Post-intervention (4 weeks) clinical, neurophysiological and DTI assessment; (4) Follow-up (8 weeks) clinical and neurophysiological assessment. Figure 1 shows the flow diagram of this study.

All stroke patients will receive a routine treatment programme including rehabilitation, medication, multidisciplinary therapy. The patient's rehabilitation included various forms of physical and occupational therapy, ~3 to 4 hours a day, 5 days a week, for 4 weeks. The intensity of active training will be appropriately adjusted according to the patient's tolerance. At the same time, an additional cTBS treatment will be provided for those participants for 4 weeks, once a day. Each patient's cTBS intervention will be performed by the same therapist.

A TMS-navigation system (Localite TMS navigator, Germany) will be used to locate the therapeutic targets, record data, and delivery the stimulation. Each patient's MRI data will be collected and imported into the navigation system to build a personalized brain model. Participants will be asked to sit in a comfortable chair with adhesive surface electrodes placed over the muscle belly and tendon of the first dorsal interosseous (FDI). The cortical target eliciting the largest responses and minimum latency of the motor evoked potential (MEP) in the first dorsal interosseous (FDI) muscle at resting status will be determined as the hotspot. The resting motor threshold (rMT) of contralesional hemisphere will be recorded accordingly, which is defined as the lowest stimulus intensity producing a MEP (peak to peak amplitude ≥ 50 μV in at least 5 of 10 trials) in the relaxed condition (30). T.M.S Motor Threshold Assessment Tool (MTAT) 2.0 (http://www.clinicalresearcher.org/software.html) will be used to assess the motor threshold (MT) (31). The location of the FDI hotspot will be set as the cTBS target for cTBS-cM1 group. As to the treatment target for cTBS-cPMA group, the dorsal portion of the superior precentral sulcus (above the superior frontal sulcus) in the contralesional hemisphere will be selected as the landmark for targeting the PMA (32). The sham group will receive cTBS with the same parameters (intensity, time) as the cTBS group on PMA of the unaffected hemisphere but with the coil rotated 90° away from the scalp so that the induced current is minimized. A transcranial magnetic stimulation (TMS MagVenture^®^ MagPro R30, Denmark) with a cool-B65 A/P figure-of-eight-shaped coil will be applied as the stimulator, and the stimulus intensity is set to 70% of contralesional hemisphere's rMT for the three groups. The participants will receive an uninterrupted 40 s train of sham cTBS stimulation over contralesional PMA or an uninterrupted 40 s train of cTBS over contralesional M1 or PMA, respectively. The basic element is a burst ofthree stimuli at 50 Hz, which is repeated at intervals of 200 ms (i.e., 5 Hz) (24), for a total of 600 pulses. Figure 2 shows the cTBS paradigm.

**Figure 2 F2:**
[figure not shown]
Continuous theta burst stimulation (cTBS) paradigm and neurophysiological effects. The basic element of cTBS is a burst of 3 stimuli at 50 Hz, which is repeated every 200 ms. In cTBS paradigm, an uninterrupted 40 s train of TBS was delivered (600 pulses).

### Tolerability and safety

Participants will be monitored during the treatment to identify any signals or adverse reactions, such as pain on stimulation site, headache, nausea, and very unlikely seizures (0.08/1,000 sessions) (33), that would require their exclusion from the study. Furthermore, any discomfort experienced by the participants will be recorded and reported.

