### Sample size calculation

Sample size is estimated through software G^*^Power 3.1 (50). We used MAS as the primary outcome for the calculation of the effect size. It is determined to be 12 per group based on a power of 0.8 with α level at 0.05. According to a previous study (21), effect size *d* = 0.53 was calculated based on the difference in MAS score from their main research results. Through conversion, the effect size *f* used in our study is about 0.25. Repeated measures correlation in our study is set at 0.5 to detect a moderate within-between effect of Conhen's *f* = 0.25. Considering a drop-out rate of 20%, we aim to recruit totally 45 stroke subjects.

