### Statistical analysis

The SPSS 21.0 program will be used for all statistical analysis and the significance level set for all the analysis will be *P* ≤ 0.05. The Shapiro-Wilk test will be used (*P* > 0.05) to check normality. In this study, Continuous variables will be expressed as mean with standard deviation and median for non-normal distributions and categorical variables will be presented as percentage or frequencies. Between the three groups, data will be first compared using Student's *t*-test for continuous variables and the chi-square or Fisher's exact tests for categorical variables. Appropriate metrics will be processed further using repeated measures ANOVA. Bonferroni correction method and False Discovery Rate <5% will be considered for multiple comparisons. All analyses will be done with the intention to treat principle, and missing data will be estimated using multiple imputation. The mean comparisons for related outcomes in two different moments will be studied with the Wilcoxon-signed rank test. The major strategy for dealing with missing data will be a sensitivity analysis and weighted estimating equations.

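### Exclusion from the study for adverse reactions is not reconciled with intention to treat, and two competing main approaches to missing data are named

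*Protocol article*

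**What the plan says.** Under Tolerability and safety, the protocol article says that participants are monitored during treatment for reactions "that would require their exclusion from the study". The examples are pain where the coil is applied, headache, nausea and, very rarely, seizure (0.08 per 1,000 sessions). The next sentence adds that any discomfort will be recorded and reported. Nothing is said about whether an excluded participant still attends later assessments.

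Under Statistical analysis, the article commits to this: "All analyses will be done with the intention to treat principle, and missing data will be estimated using multiple imputation". Two sentences later it says: "The major strategy for dealing with missing data will be a sensitivity analysis and weighted estimating equations". The model named for further analysis is repeated measures ANOVA: "Appropriate metrics will be processed further using repeated measures ANOVA".

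Two other places matter. Under Procedure, sham is delivered "with the coil rotated 90° away from the scalp so that the induced current is minimized". Under Sample size calculation, losses are budgeted: "Considering a drop-out rate of 20%, we aim to recruit totally 45 stroke subjects".

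**The concern.** Intention to treat needs outcomes, or a defensible substitute for them, from everyone randomised. A rule that ends study participation because of a reaction to stimulation removes outcomes for a reason linked to the treatment received. If such reactions are commoner with an active coil than with one turned away from the scalp, the losses fall unevenly and the active-versus-sham comparison is no longer fully protected by randomisation. Outcomes never collected at week 4, the primary time point, cannot be recovered later.

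The missing-data wording makes this worse. Multiple imputation and weighted estimating equations are different estimators with different working models and can give different answers. A sensitivity analysis tests a main analysis, so it cannot itself be the main strategy. The article does not say which result is primary.

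**Working it through.** **1. The plan's own figure.** Inputs from Sample size calculation: f = 0.25, correlation 0.5, α = 0.05, power 0.8. There are k = 3 groups and, from Table 1, m = 3 visits for the modified Ashworth scale (MAS).

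- Noncentrality = f² × N × m / (1 − ρ) = 0.0625 × 36 × 3 / 0.5 = 13.5.
- Degrees of freedom = (k − 1)(m − 1) = 4 and (N − k)(m − 1) = 66.
- Power at N = 36 is 0.823, which reproduces the stated result: "It is determined to be 12 per group based on a power of 0.8 with α level at 0.05".
- Allowing for drop-out: 36 / 0.8 = 45, so 9 losses are budgeted, or 3 per arm if spread evenly.

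The sample size is not in dispute. With 36 evaluable participants the planned test keeps power 0.82, so the issue is bias and not power.

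**2. Which reactions could matter.** Expected seizures in the two active arms = 30 participants × 20 sessions × 0.08 / 1,000 = 0.048, which is negligible. Any imbalance would come from pain, headache or nausea. The article gives no rates for these, overall or by arm.

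**3. What an excluded participant would contribute.** Table 1 schedules MAS and the Fugl-Meyer upper-extremity score (FMA-UE) at baseline, week 4 and week 8 only. Someone excluded during the 4 weeks of stimulation and not seen again has a baseline value and no later value of either primary outcome.

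**4. Illustration for completers only.** Let q be the share of an active arm that is lost, with none lost in sham. Let δ be the distance in SD between those lost and those retained in that arm. The arm's completer mean then differs from its full mean by q × δ. Both q and δ are assumptions.

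| Lost in active arm | q | δ = 0.25 | δ = 0.5 | δ = 1.0 |
|---|---|---|---|---|
| 1 of 15 | 0.067 | 0.02 SD | 0.03 SD | 0.07 SD |
| 2 of 15 | 0.133 | 0.03 SD | 0.07 SD | 0.13 SD |
| 3 of 15 | 0.200 | 0.05 SD | 0.10 SD | 0.20 SD |

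Relative to d = 0.53, the last row is 0.05/0.53 = 9%, 0.10/0.53 = 19% and 0.20/0.53 = 38%. The shift favours active treatment if those lost would have improved less than those retained, and sham if they would have improved more.

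**5. After imputation or weighting.** The same reasoning applies, with δ replaced by the part of the difference that the observed data do not explain. If they explain all of it the bias vanishes; if none, it stays. By step 3, little beyond baseline would be available to explain it.

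**6. The two missing-data sentences side by side.** One says missing values will be estimated by multiple imputation. The other gives the leading role to weighted estimating equations together with a sensitivity analysis. No sentence ranks them. Weights would also have to be estimated from about 9 losses.

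**The case against.** Several objections carry weight.

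- **Scope of the exclusion sentence.** A reader might infer that any headache or sore scalp means removal. The sentence can equally be read as covering only reactions serious enough to require exclusion, and the separate promise to record any discomfort supports that. What stands is that no threshold is stated and that, on either reading, those affected leave the study.
- **Conflict with intention to treat.** A reader might infer a flat contradiction. Leaving the study is not leaving the analysis set, and imputation is one way to keep withdrawn participants in their assigned arm. No sentence says they are dropped from the analysis. What stands is that continued assessment is not provided for.
- **Size of the bias.** A reader might take 0.05 to 0.20 SD as the bias to expect. The article does not support that. It plans imputation or weighting and not a bare completer analysis, its 20% covers drop-out from any cause with no split by arm, and the 3-versus-0 split is an assumption. That reactions are commoner with active stimulation is plausible from the sham set-up but is not documented.
- **Choice made after seeing results.** A reader might infer that the primary estimate will be picked once results are known. An analysis plan not shown here may settle it, and Randomization and blinding says data analysts are blind to allocation. What stands is that the published text gives two main approaches, which is an inconsistency and not an omitted detail.

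**Conclusion.** The point holds in a limited form. The exclusion wording and the intention-to-treat commitment are not reconciled: as written, week-4 primary outcomes can be lost for a reason that could plausibly differ by arm. The article also names two competing main approaches to missing data.

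The size and direction of any bias cannot be determined from the article. The 0.05 to 0.20 SD shift rests on assumed losses (3 of 15 in one active arm, none in sham), an assumed difference of 0.25 to 1.0 SD between those lost and those retained, and an analysis of completers only. It shows that the issue can be non-trivial next to d = 0.53; it is not a forecast. The point should be corrected, but it does not invalidate the design or the sample size.

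**What to change.** - **Reconcile Tolerability and safety with Statistical analysis.** Leave the existing safety rule as it is. State that participants whose stimulation ends under it are still invited to the week-4 and week-8 assessments and are analysed in their assigned arm. This should be settled before any exclusion occurs.
- **Name one primary missing-data method, applied to the planned analysis.** One workable choice is multiple imputation with a small model pooled over arms, containing arm, baseline and other-visit values of the same outcome, with MAS either collapsed or handled per muscle group. Imputing separately by arm from everything recorded is not advisable. Four muscle groups × 3 visits plus 3 FMA-UE scores gives 15 variables, against 12 to 15 participants per arm.
- **List weighted estimating equations, if kept, only as a sensitivity analysis.**

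The cost is revised wording, a few extra visits by participants already counted in the 45, and slightly more analysis work. The target stays at 36 evaluable and 45 recruited.

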### Outcome measurements

The primary outcomes are MAS and FMA-UE. Changes before and after the 4 weeks of treatment will be used as the primary measure to assess improvement in spasticity and abnormal movement synergies (9). And the secondary outcomes are results from neurophysiological examinations including H reflex, M response, MEP and SR, and changes of neuroimaging with DTI.

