**Methods:**

This trial is a single-center, prospective, three-group randomized controlled trial. Forty-five eligible patients will be recruited and randomized into three groups: the sham-cTBS group (sham cTBS targeting contralesional PMA), the cTBS-cM1 group (cTBS targeting contralesional M1), and the cTBS-cPMA group (cTBS targeting contralesional PMA). All subjects will undergo comprehensive rehabilitation and the corresponding cTBS interventions once a day, five times a week for 4 weeks. Clinical scales, neurophysiological examinations, and neuroimaging will be used as evaluation tools in this study. As the primary outcome, clinical performance on muscle spasticity of elbow/wrist flexor/extensors and upper-limb motor function will be evaluated with the modified Ashworth scale and the Fugl-Meyer Assessment of Upper Extremity Scale, respectively. These scale scores will be collected at baseline, after 4 weeks of treatment, and at follow-up. The secondary outcomes were neurophysiological examinations and Neuroimaging. In neurophysiological examinations, motor evoked potentials, startle reflex, and H reflexes will be used to assess the excitability of the subject's motor cortex, reticulospinal pathway, and spinal motor neurons, respectively. Results of them will be recorded before and after the first cTBS treatment, at post-intervention (at 4 weeks), and at follow-up (at 8 weeks). Neuroimaging tests with diffusion tensor imaging for all participants will be evaluated at baseline and after the 4-week treatment.

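### The 12 per group is reproduced only by a three-visit interaction, whereas the primary measure is a two-visit change, for which 36 completers give about 73% power if f = 0.25 is the two-visit effect

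*Protocol article*

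**What the plan says.** Under Outcome measurements, the protocol names MAS and FMA-UE as primary and fixes the window: "Changes before and after the 4 weeks of treatment will be used as the primary measure". That is one value before and one after treatment.

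Under Sample size calculation, G*Power 3.1 is applied to MAS. The result is given as "It is determined to be 12 per group based on a power of 0.8 with α level at 0.05". The effect size starts from d: "0.53 was calculated based on the difference in MAS score from their main research results". After conversion, the f "used in our study is about 0.25". The test is identified by "Repeated measures correlation in our study is set at 0.5 to detect a moderate within-between effect". A 20% drop-out allowance takes the total to 45. The number of repeated measurements, which this G*Power procedure requires, is not given.

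On the schedule, the abstract says of MAS and FMA-UE: "These scale scores will be collected at baseline, after 4 weeks of treatment, and at follow-up". Table 1 and the clinical assessments section agree, so MAS is measured three times. The Statistical analysis section names repeated measures ANOVA without saying which visits enter it.

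**The concern.** In a within-between interaction, the number of measurements changes both the noncentrality and the degrees of freedom, so one f and one correlation give different sample sizes for two, three or four visits. If the 12 per group was obtained with three visits, the 80% belongs to a 4-df test that includes week 8, not to the 4-week change declared as primary.

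Two things are at stake. The false-negative risk for the declared primary measure may be above the stated 20%. The two tests also ask different questions. The three-visit interaction can be significant because the arms separate during the off-treatment weeks 4 to 8, and it can miss a week-4 difference that partly wanes.

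**Working it through.** **Inputs.** Three equal groups (Study design); f = 0.25, correlation ρ = 0.5, α = 0.05, target power 0.80 and 20% drop-out (Sample size calculation). The number of measurements m is not stated and is varied here. No sphericity correction is mentioned, so ε = 1 is assumed; for m = 2 it has no effect.

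**Formula.** This is the G*Power option that takes a correlation among repeated measures:

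- λ = f² · N · m / (1 − ρ)
- df1 = (k − 1)(m − 1), df2 = (N − k)(m − 1), with k = 3
- power = P(noncentral F(df1, df2, λ) > F at 1 − α)

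**Reproducing the plan's figure.** Smallest n per group with power of at least 0.80:

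| m | n per group | N | power |
|---|---|---|---|
| 2 | 14 | 42 | 0.803 |
| 3 | 12 | 36 | 0.823 (11 per group: 0.781) |
| 4 | 10 | 30 | 0.809 |
| 5 | 9 | 27 | 0.817 |

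Only m = 3 returns 12. Then 36 / (1 − 0.2) = 45, the stated total.

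**Power at 36 completers.**

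- m = 3: λ = 0.0625 × 36 × 3 / 0.5 = 13.5; df 4 and 66; power 0.823.
- m = 2: λ = 0.0625 × 36 × 2 / 0.5 = 9.0; df 2 and 33; power 0.729.

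A one-way ANOVA on the change score gives the same 0.729. With ρ = 0.5, an interaction f of 0.25 corresponds to f = 0.5 on the change, and 0.25 × 36 = 9.0 is the same λ.

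**Sensitivity of the two-visit figure.**

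- Unrounded f = d/2 = 0.53/2 = 0.265: λ = 10.11, power 0.781 at 36; 13 per group would be needed. At this f the three-visit calculation would return 11 per group, so the stated 12 points to f = 0.25 having been entered.
- All 45 evaluable, f = 0.25: λ = 11.25, df 2 and 42, power 0.834.
- f giving power 0.80 at N = 36: 0.271.

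**If f = 0.25 is instead a three-visit effect.** Assume one arm differs from the other two, by δ at week 4 and rδ at week 8. The variance over visits of the profile (0, 1) is 1/4, and that of (0, 1, r) is 2(1 − r + r²)/9. Hence f₃²/f₂² = 8(1 − r + r²)/9. Setting f₃ = 0.25 at N = 36:

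| r (share left at week 8) | two-visit f | two-visit power |
|---|---|---|
| 0 or 1 | 0.265 | 0.782 |
| 0.25 or 0.75 | 0.294 | 0.864 |
| 0.50 | 0.306 | 0.891 |
| 1.25 | 0.231 | 0.658 |

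In the other direction, with the two-visit f fixed at 0.25, the three-visit f is 0.236 (power 0.77) for r = 0 or 1 and 0.204 (power 0.63) for r = 0.5.

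**The case against.** The strongest reply is that f is not the same quantity over two visits and over three. Applying 0.25 to the two-visit change reassigns it to a scale the sample size section does not name. If 0.25 was meant over three visits, a lasting or waning effect leaves the week-4 comparison with about 78% to 89% power. This stands: 73% is conditional, and a reader who takes it as the trial's power without qualification goes further than the document allows.

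A reader might also infer that the protocol defines two competing primary windows. It does not. Only Outcome measurements defines a window; the abstract and Table 1 give collection times, and the sample size section is silent. The three-visit setting is inferred from the arithmetic. A two-visit main effect of time also returns 36, but it does not compare groups and is not the effect named.

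Two further replies carry some weight. The shortfall is moderate, it assumes the full 20% loss, and the trial is described as a pilot. Which visits enter the ANOVA could also be left to an analysis plan. Neither removes the point. The protocol itself prints a sample size, a power and a primary window, and on its printed inputs the first two do not follow for the third.

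**Conclusion.** The point holds in limited form. The claim of 80% power at 12 per group does not follow from the stated inputs for the baseline-to-week-4 change, which needs 14 per group. It follows for a three-visit interaction that the protocol does not name as primary.

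The size depends on what f = 0.25 refers to. As a two-visit effect, the shortfall is about 7 points (72.9% against 80%), a false-negative risk of about 27% at 36 completers. It shrinks to about 2 points at f = 0.265 and vanishes if nobody drops out. As a three-visit effect, there may be a shortfall or none, depending on the week-8 profile. All figures assume the named test, ρ = 0.5 and, for three or more visits, sphericity; the profile figures also assume that only one arm differs. The arithmetic is certain; the three-visit setting is a well-supported inference.

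**What to change.** In Sample size calculation, state that the number of measurements is two, to match Outcome measurements, and that f refers to the group-by-time effect from baseline to week 4. Restate the power as about 73% at f = 0.25 with 12 completers per group, or give the detectable effect as f of about 0.27 for 80%. Keep 45 patients. Label week 8 and the three-visit interaction as secondary. Amending the abstract so that follow-up is not read as part of the primary outcome is optional.

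The change is to wording only, with no extra patients or visits. Its cost is a less favourable stated power. Holding 80% at f = 0.25 would instead need 42 completers, that is 42 / 0.8 = 52.5, so 53 recruited, or 54 for equal groups.
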